## Abstract

**Background:**

Even today, treatment of Stage III NSCLC still poses a serious challenge. So far, surgical resection is the treatment of choice. Patients whose tumour is not resectable or who are unfit to undergo surgery are usually referred to a combined radio-chemotherapy. However, combined radio-chemotherapeutic treatment is also associated with sometimes marked side effects but has been shown to be more efficient than radiation therapy alone.

Nevertheless, there is a significant subset of patients whose overall condition does not permit administration of chemotherapy in a combined-modality treatment.

It could be demonstrated though, that NSCLCs often exhibit over-expression of EGF-receptors hence providing an excellent target for the monoclonal EGFR-antagonist cetuximab (Erbitux^®^) which has already been shown to be effective in colorectal as well as head-and-neck tumours with comparatively mild side-effects.

**Methods/design:**

The NEAR trial is a prospective phase II feasibility study combining a monoclonal EGF-receptor antibody with loco-regional irradiation in patients with stage III NSCLC. This trial aims at testing the combination's efficacy and rate of development of distant metastases with an accrual of 30 patients.

Patients receive weekly infusions of cetuximab (Erbitux^®^) plus loco-regional radiation therapy as intensity-modulated radiation therapy. After conclusion of radiation treatment patients continue to receive weekly cetuximab for 13 more cycles.

**Discussion:**

The primary objective of the NEAR trial is to evaluate toxicities and feasibility of the combined treatment with cetuximab (Erbitux^®^) and IMRT loco-regional irradiation.

Secondary objectives are remission rates, 3-year-survival and local/systemic progression-free survival.

## Background

80% of all lung cancers are non small cell carcinomas. For these tumours, complete surgical resection still yields the best treatment results so far. However, only 25% of all patients have the option of surgical treatment.

In the event of the tumour being surgically not resectable or the patient functionally inoperable, radiation therapy/combined radio-chemotherapy are the only curative treatment options for lung cancer in a localised stage. In this case, a dose of 60–66 Gy is usually applied to the tumour by external beam radiotherapy (EBRT) resulting in a mean local tumour control of about 12 months [1]. Furthermore, a recent meta-analysis was able to demonstrate improved results in combined radio-chemotherapy on platinum-based regimen with a significantly higher 2-year-survival compared to local irradiation alone [2]. It could also be shown in various randomised trials that simultaneous platinum-based radio-chemotherapy is significantly superior to sequential regimen [3-5]. Accompanying toxicities are, however, not negligible, especially considering the simultaneous radio-chemotherapy [3] which is the reason for many patients proving ineligible for a combined treatment.

Other potential partners for combined treatment are monoclonal antibodies. NSCLCs often show an over-expression of epidermal growth factor receptors (EGFR) [6,7] also associated with a less favourable prognosis. In pre-clinical experiments EGFR inhibition was able to show a reduction of cell proliferation, an increase of apoptosis, and a reduction of angiogenesis [8,9].

Cetuximab is a monoclonal antibody which binds to the extracellular EGF-receptor domain hence inhibiting intracellular phosphorylation of EGFR and consecutive down stream signalling. This in turn causes cell cycle arrest and increased expression of pro-apoptotic enzymes.

Combining irradiation and cetuximab exposure, a synergistic and/or additive effect could be demonstrated in NSCLC cell lines in vitro [10].

In the case of squamous cell carcinoma of the head and neck, a G_0_/G_1_-cell cycle arrest could be observed with the radiation-induced damage exhibiting a reduction of repair and an increase in apoptosis compared to irradiation alone [9-11].

There are various phase I-III trials which were able to demonstrate that cetuximab can be safely administered as a single drug and also in combination with irradiation [14-19].

In a large phase III trial, patients with head and neck tumours were randomized either to irradiation alone or in combination with cetuximab. 424 patients were enrolled in this trial showing a significantly higher 3-year survival of 55% in the combined treatment vs. 45 % for irradiation alone [18]. These encouraging results show a good correlation to results obtained in combined radio-chemotherapy vs. irradiation alone in locally advanced head and neck cancer [20]. However, combining irradiation and cetuximab also resulted in an increase of skin reactions [18].

In conclusion, there are good reasons to expect improvement of treatment results with respect to local tumour control and acceptable toxicity on combining irradiation and application of EGF-receptor antibodies.

The main purpose of the NEAR-trial (**N**on-small cell lung cancer, **E**rbitux **A**nd **R**adiotherapy) is to evaluate the feasibility and safety of a new treatment regimen in inoperable NSCLC stage III by combining loco-regional irradiation and weekly application of the monoclonal EGFR- receptor antibody cetuximab (Erbitux^®^) in patients who are not eligible for a radio-chemotherapy.

## Methods/design

### Trial organization

NEAR has been designed by the Trial Center of the Department of Radiation Oncology, University of Heidelberg in cooperation with the Thoraxklinik in Heidelberg. The trial is carried out by the Department of Radiation Oncology together with the German Cancer Research Center (DKFZ) and Department of Medical Oncology of the Thoraxklinik Heidelberg. The trial is an investigator initiated trial. Trial medication (cetuximab) is supplied by Merck KGaA, Darmstadt, Germany.

### Coordination

The trial is co-ordinated by the Department of Radiation Oncology of the University of Heidelberg in cooperation with the DKFZ and the Department of Medical Oncology at the Thoraxklinik Heidelberg. The Dept. of Radiation Oncology is responsible for overall trial management, trial registration (ClinicalTrials.gov Identifier: NCT00115518), database management, quality assurance including monitoring, reporting and for the scientific program of all trial related meetings.

### Investigators

Patients will be recruited by the Department of Radiation Oncology at the University of Heidelberg and by the Department of Medical Oncology of the Thoraxklinik Heidelberg. Due to the multi-modal nature of the trial, all investigators are experienced oncologists from the fields of radiation oncology and medical oncology.

### Adverse events committee

This committee consists of 2 physicians (medical oncologist, radiation oncologist) and decides on the final diagnostic classification of critical clinical events. For all serious adverse events the documentation and relevant patient data are verified by the co-ordinating personnel before submitting the data to the Adverse Events Committee for diagnostic classification.

Analysis of safety related data is performed with respect to frequency of:

• Serious Adverse Events and Adverse Events stratified by organ-system

• Adverse Events stratified by severity

• Adverse Events stratified by causality.

Patient toxicities will be assessed using the NCI Common Toxicity Criteria (CTC). Toxicity will be evaluated prior to treatment, weekly prior to each course of infusional Cetuximab and at follow-up. Unacceptable toxicity is defined as unpredictable, or irreversible Grade 4 toxicity. Decisions regarding cetuximab dose-adjustment will be made using the guidelines below and based on haematological parameters (ANC and platelets) monitored weekly during radiation before each dose of cetuximab.

### On-site monitoring

During recruitment of patients monitoring on site is performed according to good clinical practice (GCP) guidelines. The data management will be performed by the Trial Centre of the Department of Radiation Oncology, University of Heidelberg.

### Ethics, informed consent and safety

The final protocol was approved by the ethics committee of the University of Heidelberg, Medical School (L-284/2004) and the Paul-Ehrlich-Institute ((PEI-registration number 1209/01). This study complies with the Helsinki Declaration in its recent German version, the Medical Association's professional code of conduct, the principles of Good Clinical Practice (GCP) guidelines and the Federal Data Protection Act. The trial will also be carried out in keeping with local legal and regulatory requirements. The medical secrecy and the Federal Data Protection Act will be followed.

Written informed consent is obtained from each patient in oral and written form before inclusion in the trial and the nature, scope, and possible consequences of the trial have been explained by a physician. The investigator will not undertake any measures specifically required only for the clinical trial until valid consent has been obtained.

### Study design

The NEAR-study is a prospective phase II feasibility study combining a monoclonal EGF-receptor antibody with loco-regional irradiation in patients with stage III NSCLC. This trial aims at testing the combination's safety and efficacy and rate of development of distant metastases with an accrual of 30 patients. These are treated by the Dept. of Radiation Oncology and Radiation Therapy, University of Heidelberg, in co-operation with the German Cancer Research Centre (DKFZ), Heidelberg, the Dept. of Medical Oncology, Thoraxklinik, Heidelberg, and the Dept. of Nuclear Medicine, University of Heidelberg.

Primary endpoints are toxicities and feasibility of the combined treatment.

Secondary endpoints are remission rates, 3-year-survival and local/systemic progression-free survival.

### Patient selection

In order to be included in the NEAR trial, patients were required to have histologically confirmed NSCLC and documented inoperable NSCLC stage III disease, where combined chemo-radiotherapy is either deemed medically contra-indicated or refused by the patient. Each patient is discussed by a commitee consisting of a thoracic surgeon, a medical oncologist, a pulmonologist, a radiologist and a radiation oncologist. Evaluation of EGFR status is recommended but not compulsory. Patients also need to have sufficient remaining lung function (FeV_1 _≥ 1.5 l/s or at least 50% of the respective individual norm value) as well as a Karnofsky Performance score of 70 % or higher.

Patients should be ≥ 18 years and individual life expectancy be estimated to ≥ 6 months. Accrued patients will be expected to demonstrate sufficient compliance, they should also live in relative proximity of the centre of care to ensure adequate follow-up after treatment. In addition, adequate haematological, hepatic, and renal function is essential for inclusion in the trial (wbc ≥ 3000 × 10^3 ^/ml, thc ≥ 100 × 10^6 ^/ml, hb ≥ 10 g/dl).

Female patients are required to use adequate contraception during and at least up to 3 months after treatment. Naturally, written informed consent is obtained prior to commencement of treatment in this trial.

Patients are not eligible with active infections, inadequate liver function (bilirubin ≥ 2 × above normal, GOT/GPT > 5 × above normal) or haemodynamically relevant haemoptyses (hb-drop of 1 g/dl within 24 h), superior vena cava syndrome, or malignant pleural effusions. Patients with severe concurrent systemic disease or other malignant disease (apart from cervical carcinoma in-situ, basal cell carcinoma, or unless previously treated and in remission for ≥ 5 years without further treatment) can also not be included in this trial. Furthermore, hypersensitivity to foreign proteins or x-ray contrast medium, or use of other test substances within one month prior to commencement of the NEAR trial and previous chemotherapy will prohibit inclusion as will pregnancy or breast feeding.

### Work-up

Patients with pathologically or cytologically documented NSCLC stage III receive a complete work-up including thoracic and cerebral CT scans, abdominal ultrasound, bone scan (plus x-ray exams of suspect areas where applicable). Patients with positive mediastinal lymph nodes, (either pathologically documented or found suspect in the CT-scan due to diameter >1.5 cm) will be sent for surgical consultation and evaluation of operability. Should operation be found impossible, in,-and exclusion criteria are examined. In the event of patients meeting the required inclusion criteria, information about participation in the study with possible risks and benefits is given to the patients and written informed consent is obtained. Patients can then be included in the study, documentation is provided by the study centre (Studienzentrale Klinische Radiologie, Abt. Strahlentherapie und Radioonkolgie, [name]).

After inclusion, patients are referred to FDG-PET scanning in order to optimise target volume definition. Each patient receives a radiation therapy planning CT-scan in individually-adjusted precision immobilisation devices.

In the event of patients declining treatment within the NEAR trial, irradiation alone is offered.

### Safety and discontinuation of treatment

Toxicities are classified by grade, type, duration, onset, and relationship to study treatment.

Treatment of cetuximab-induced adverse reactions is carried according to recommendations by the provider.

For grade 1 or 2 allergic reactions, a decrease of infusion rate for current and subsequent infusions is suggested. For ≥°3, persistent °1 or °2 allergic reactions despite reduction of infusion rate, it is recommended to discontinue treatment with cetuximab. Skin reactions in terms of acne-like rash after cetuximab are common. In patients with °3 acne-like rash cetuximab should be delayed for up to two subsequent infusions. Treatment also includes concomitant topical and/or oral antibiotics where necessary. Therapy can be resumed on resolution of the rash to <°2. Cetuximab needs to be delayed on a 2^nd ^or 3^rd ^occurrence of a °3 skin reaction for up to two consecutive cycles with dose reduction to 200 mg/m^2 ^or 150 mg/m^2 ^respectively. Any further occurrence of grade °3 acne-like rash will lead to discontinuation of cetuximab treatment.

### Drug supply

The monoclonal antibody cetuximab (Erbitux^®^) is provided by Merck KGaA, Darmstadt, Germany, and stored by the University Hospital Pharmacy, Heidelberg.

The respective cetuximab dose applied in this setting corresponds to the recommended and approved dosage tested in combination with irinotecan in metastatic colo-rectal carcinoma [19]. Cetuximab is given with a loading dose of 400 mg/m^2 ^as an intravenous infusion on day 1. Subsequently, the regular weekly dose during radiotherapy is 250 mg/m^2 ^on days 8, 15, 22, 29, 36, 43, and 50. After completion of irradiation, patients continue to receive 250 mg/m^2 ^weekly for another 13 weeks. Administration of cetuximab is discontinued if patients show local or systemic progression.

### Radiation therapy

Irradiation is applied as intensity-modulated radiation therapy (IMRT). The primary tumour and mediastinal lymph nodes receive a dose of 50 Gy in daily fractions of 2 Gy (Monday to Friday).

Primary tumour and involved lymph nodes are subsequently boosted to a total dose of 66 Gy in daily fractions of 2 Gy. Tolerances of thoracic organs at risk should not be exceeded.

The schedule of the treatment is shown in Figure 1:

### Supportive therapy

Whenever necessary, metoclopramide or 5-HT_3_-antagonists are used for antiemesis.

Antihistamines such as clemastine or dimetinden and steroids are administered prior to cetuximab-application. Skin reactions, especially acne-like rashes can be treated by topic or systemic antibiotics (i.e. tetracyclines or metronidazole) if necessary. Radiation induced skin reactions are treated according to in-house protocols with mild moisturizing lotion (i.e. Bepanthen^®^-lotio) or local application of steroids.

### Trial duration

Individual participation is completed either three years after enrolment or death of the patient.

Individual exclusion criteria are serious adverse reactions or the patient's voluntary withdrawal from the trial.

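### As worded, a serious adverse reaction ends trial participation, so later toxicity, progression and survival follow-up may be lost in the patients who matter most for the primary endpoint

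*Protocol article*

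**What the plan says.** All references are to the protocol article.

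- **Trial duration** sets the normal end of participation: "Individual participation is completed either three years after enrolment or death of the patient". The next sentence adds: "Individual exclusion criteria are serious adverse reactions or the patient's voluntary withdrawal from the trial".
- **Study design** plans 30 patients and states: "Primary endpoints are toxicities and feasibility of the combined treatment". It continues: "Secondary endpoints are remission rates, 3-year-survival and local/systemic progression-free survival".
- **Adverse events committee** gives the assessment times: "Toxicity will be evaluated prior to treatment, weekly prior to each course of infusional Cetuximab and at follow-up". It counts irreversible Grade 4 toxicity as unacceptable, and its planned safety tables include "Serious Adverse Events and Adverse Events stratified by organ-system".
- **Safety and discontinuation of treatment** lists duration among the features by which each toxicity is classified. For severe allergic reactions and severe rash, its consequences concern the drug only, for example: "Any further occurrence of grade °3 acne-like rash will lead to discontinuation of cetuximab treatment".
- **Assessment of therapeutic efficacy** schedules chest CT every 3 months, abdominal ultrasound every 6 months and a bone scan every 12 months up to the end of the study. It makes no exception for patients who had a serious reaction.

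**The concern.** The exclusion sentence does not distinguish stopping cetuximab from leaving the trial. It pairs serious adverse reactions with withdrawal from the trial, directly after the rule on how long participation lasts. A site following it as written would stop observing a patient at the moment a serious reaction occurs.

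The exit would then depend on the primary endpoint. Whether a reaction resolves, how long it lasts and whether late toxicity follows can be learned only by continued observation. Progression and 3-year survival would also go unobserved in these patients. Their prognosis may well differ from that of the others, so the loss is plausibly informative. An analysis plan can choose how to handle missing data, but it cannot recover data that were never collected.

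**Working it through.** **Step 1: what the sentence governs.**

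- *Entry to the trial?* No. Eligibility is set out under Patient selection, and a reaction to study treatment cannot precede entry.
- *Stopping the drug only?* Unlikely from the wording. Safety and discontinuation of treatment and Drug supply already cover delaying, reducing or stopping cetuximab, and they name the drug each time. The sentence under Trial duration does not name it.
- *Leaving the trial?* This is the plain reading, given the heading, the preceding sentence and the pairing with withdrawal.

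**Step 2: comparison with the other sections.**

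| Section | What it needs after a serious reaction | If participation ends |
|---|---|---|
| Adverse events committee | Toxicity assessment at follow-up; a judgement on irreversibility | Not possible after exit |
| Safety and discontinuation of treatment | Duration of each toxicity; consequences limited to the drug | Duration cut short; consequence differs |
| Assessment of therapeutic efficacy | Imaging to the end of the study | Stops early |
| Study design | 3-year survival, progression-free survival | Unknown after exit |

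The triggering event itself is not lost. The Adverse events committee section has every serious event documented, verified, classified and tabulated.

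**Step 3: size.** The article states no figure to reproduce. From the document: N = 30 and follow-up of three years. Assumed: the share of patients with a serious adverse reaction, and all outcome rates.

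*Best/worst-case range for 3-year survival.* If k patients have unknown outcome and x of the rest survive, the proportion lies between x/30 and (x + k)/30, a width of k/30. Each patient adds 1/30 = 3.3 points.

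*Overstatement if only retained patients are used.* With survival s0 in retained and s1 in excluded patients, the all-patient rate is [(30 − k)·s0 + k·s1]/30, and the overstatement is (k/30)(s0 − s1). Take s0 = 30% and s1 = 10%:

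| Assumed share | k | Retained | Range width | All 30 | Retained only | Overstatement |
|---|---|---|---|---|---|---|
| 10% | 3 | 27 | 10 points | 28% | 30% | 2 points |
| 20% | 6 | 24 | 20 points | 26% | 30% | 4 points |
| 30% | 9 | 21 | 30 points | 24% | 30% | 6 points |

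If s1 = s0, the overstatement is zero in every row.

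*Precision.* The standard error is √[p(1 − p)/n]. With all 30 patients it is 0.082, 0.080 and 0.078 for p = 0.28, 0.26 and 0.24. With retained patients only (p = 0.30; n = 27, 24, 21) it is 0.088, 0.094 and 0.100.

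*Late toxicity.* Assume a 20% reaction share, with late toxicity in 10% of retained and 30% to 50% of excluded patients. The all-patient rate is (24 × 10% + 6 × 30%)/30 = 14%, up to (24 × 10% + 6 × 50%)/30 = 18%. Retained patients show 10%, which is 4 to 8 points too low.

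*Chance of seeing at least one case of a 10% late toxicity.* This is 1 − 0.9ⁿ: 95.8% for n = 30, 94.2% for 27, 92.0% for 24 and 89.1% for 21.

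**The case against.** **Loss of follow-up is inferred.** The sentence never says that assessments, imaging or vital status stop. The authors may have meant stopping treatment, and the full protocol may say so. This stands as a limit on certainty. It does not remove the point, because the article states a rule whose plain meaning is exit and nothing in it says otherwise. The imaging schedule does not settle the matter either: its end point, completion of the study, can be read for the trial or for the individual patient.

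**The toxicity endpoint is largely protected.** A reader might infer that serious reactions drop out of the toxicity rate, even to zero, or that these patients leave the denominators. The document does not support this. The triggering event is tabulated, and no section removes anyone from an analysis. Analysis sets belong to the analysis plan, which is not shown. This objection stands, and the point is confined to what happens after the event.

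**The numbers are assumed and modest.** This also stands. A reader might infer that survival is certainly biased upward, but that requires worse outcomes in the excluded patients. On the figures used, the 2 to 6 points are smaller than one standard error (about 8 to 10 points), and the article states no threshold they could overturn. The calculation also models complete removal rather than censoring at exit.

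**Withdrawal.** A patient's withdrawal from the trial is a decision about participation, so ending participation then is no fault. Finer distinctions between partial and full withdrawal are details an article commonly omits.

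**Conclusion.** The point holds as a conflict within the document. The sentence under Trial duration, followed as written, ends participation because of a primary-endpoint event, while other sections need the same patients observed further. At risk are later toxicity, reversibility, progression and 3-year survival in patients with a serious adverse reaction. The record of the reaction itself is not at risk.

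The size cannot be derived from the document. The range width of 10 to 30 points rests only on an assumed 10% to 30% of patients leaving with unknown outcome. The overstatement of 2 to 6 points rests in addition on assumed survival of 10% against 30%. The possible bias is small next to sampling error, so the case for correction is that the loss would be irrecoverable, tied to the primary endpoint, and easy to prevent.

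**What to change.** Reconcile Trial duration with Adverse events committee, Safety and discontinuation of treatment, and Assessment of therapeutic efficacy. Amend the exclusion sentence to say that:

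- a serious adverse reaction does not end trial participation;
- all enrolled patients stay in the toxicity, imaging and survival follow-up already scheduled until three years, death or withdrawal of consent to follow-up itself.

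No change to any dose or treatment-stopping rule is proposed. If the full protocol already says this, the article's wording only needs to be brought into line.

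The cost is one amended sentence. The assessments are already in the schedule, so no new procedure is needed.
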